### Sample size {14}

Sample size calculations are based on the primary endpoint (the proportion of clinical improvement within 7 days after randomization). At the 5% significance level, a total of 101 patients per group is required to achieve 90% power and to determine an increase of 20% in the proportion of clinical improvement between *QZQG* group and the placebo group, assuming that the clinical improvement rate within 7 days after randomization of the placebo group receiving oseltamivir plus routine symptomatic treatment is about 50%. With an estimated dropout rate of 10–20%, a total of 228 patients are planned to be enrolled. If the initial hypothesis is not rejected, subsequent comparison is considered exploratory, and no conclusion is made.

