## Assignment of interventions: allocation

### Sequence generation{16a}, concealment {16b}, and implementation {16c}

According to a stratified block randomization method, all patients are stratified by study center and randomly assigned to the *QZQG* group and placebo group in a 1:1 ratio. The random sequence and the randomization list of every center will be generated by the independent specialist from School of Public Health, Fudan University, China using the PRCO PLAN function of the analysis system of SAS software (SAS, Cary, NC, USA). The randomization sequence will be concealed in a lightproof sealed envelope for emergency unblinding events, which will be kept by the independent specialist and the Sponsor. An independent drug administrator at every center will assign numbered packs of study drugs to eligible patients in order by randomization list.

An emergency letter including the random sequence and assignment has been prepared in all of centers. In any emergency medical situation, such as serious adverse event or deteriorative condition, the unblinding process will be started after contacting the Sponsor and the primary investigator. The investigators from Longhua Hospital Affiliated to Shanghai University of traditional Chinese Medicine will record the details of urgent unblinding and make sure the corresponding patient is excluded. If the rate of drug blinding leakage or emergency letter opening rises more than 20%, this trial will be considered as failure.

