### Circumstances and procedure for unblinding if needed {17b}

Unblinding is permissible in emergency situations when investigators believe that it is necessary to perform any agent treatment/action for the trial patient’s safety. To allow emergency unblinding the investigator will be supplied with a set of emergency envelopes. If emergency unblinding of a patient is necessary, an independent pharmacist opens the sealed envelope and informs the investigators of the allocation. And the pharmacist has to enter date and time as well as his/her name and signature on the unblinding form contained in the envelope. Information about the date, time, and reason of unblinding will be recorded in Clinical Case Forms (CRFs) and the envelope.

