## Statistical methods

### Statistical methods for analyzing primary and secondary outcomes {20a}

The primary study analysis will occur when the last patient has either withdrawn or completed day 28 visit, and will be based on cleaned data for all patients up to and including this point. The clinical data will be managed and analyzed by the independent statisticians from a third party (School of Public Health, Fudan University,) in accordance with the statistical analysis plan. Data management and analysis will use SAS V.9.4 (SAS Institute, Cary, NC, USA).

All statistical inferences will be determined using two-sided tests. *P* < 0.05 will be considered significant, and 95% confidence intervals will be used. Data will be described as the mean, standard deviation, and confidence intervals. If necessary, minimum, maximum, P25, P75, and median values will be provided. Paired measurement data will also show the differences between the mean and standard deviation. When using nonparametric methods, median and mean values will be provided. Count data will be described using the frequency distribution and corresponding proportion. Qualitative information will be described using the positive rate, the number of positive cases, and the denominator.

Baseline data analyses (in FAS and PPS) will include demographic indicators and primary and secondary outcomes before intervention. Measurement data will be described using a *t*-test or *t*’ test (if the variance is absent). Count data will be described using the Pearson’s *χ*^2^ test. Rating data will be described using the two-sample Wilcoxon rank sum test.

Logistic regression model will be used to explore the efficacy (*QZQG* group and placebo group) and factors affecting efficacy. Dependent variable is the proportion of clinical improvement at day 7. In addition to drugs, independent variables also include the basic information and life behavior factors of participants. The basic information includes gender, height, weight, age, and underlying diseases that include chronic obstructive pulmonary disease, asthma, diabetes, hypertension, hyperlipidemia, hyperuricemia, cardiovascular disease, autonomic nervous dysfunction, lung cancer, other tumors, etc. Life behavior factors mainly include smoking and drinking.

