### Definition of analysis population relating to protocol nonadherence {20c}

The intent-to-treat (ITT) population is defined as all randomized patients, whether or not the patient received the assigned treatment. The ITT patients will be analyzed according to the treatment assigned at randomization. The ITT population includes the patients who agree to enroll in the study and sign an informed consent form. However, ITT population involves those who have never received study drugs or never completed observation records. Efficacy analyses will be conducted for the modified intent-to-treat (mITT) population. This is defined as all patients randomized who received at least one dose of *QZQG* formula and were centrally assessed as RT-PCR positive for influenza at any timepoint, with patients grouped according to the treatment assigned at randomization. The per-protocol set is used to analyze the main outcome for evaluating efficacy and to examine the consistency of the results from the mITT. The PPS is defined as follows: (1) full compliance with inclusion and exclusion criteria; (2) the compliance of medication consumption is over 80%; (3) the patients complete the test and record of the outcome and safety evaluation at every time node; and (4) completion of the clinical trial without major protocol violation. The safety analysis set (SAS) is defined as patients who received any amount of study treatment. Patients will be analyzed according to the treatment received. Patients who were randomized to the study but who did not receive any study drug will not be included in the safety population. The SAS will be used for the analysis of all safety indicators. Multiple imputation will be used for missing data.

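### One pooled unblinding rate above 20% labels the whole trial a failure, whatever the arm, the timing or the primary result

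*Protocol article*

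**What the plan says.** All of the following is in the protocol article.

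- **Section {16a}–{16c}, the rule:** "If the rate of drug blinding leakage or emergency letter opening rises more than 20%, this trial will be considered as failure".
- **Same section, what leads to letter opening:** "In any emergency medical situation, such as serious adverse event or deteriorative condition, the unblinding process will be started", after contact with the sponsor and the primary investigator.
- **Same section, the unblinded patient:** the coordinating site records the details and must "make sure the corresponding patient is excluded".
- **Section {17b}, a softer condition:** "Unblinding is permissible in emergency situations when investigators believe that it is necessary to perform any agent treatment/action for the trial patient’s safety". Date, time and reason are recorded in the CRF and on the envelope.
- **Section {20c}, populations:** "The intent-to-treat (ITT) population is defined as all randomized patients, whether or not the patient received the assigned treatment", and "The ITT patients will be analyzed according to the treatment assigned at randomization". Efficacy analyses are assigned to the mITT set.
- **Outcomes and timeline:** the primary outcome is clinical improvement within 7 days, while visits run to day 28.

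The article does not define 'failure'. It does not state the denominator of the rate, or whether leakage and letter openings are added together or each compared with 20%. It does not derive the 20% from anything.

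**The concern.** A rate of broken blinding says something about how far a result can be trusted. This rule instead turns it into a verdict on the whole trial, and the rate is a poor basis for that in four ways.

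1. **It depends on outcome.** Letter opening is linked to serious adverse events and deterioration. Deterioration lies close to the opposite of the primary endpoint, so in severe influenza the opening rate partly measures prognosis and treatment effect. This applies to letter opening only; the text does not tie leakage to deterioration.
2. **It is pooled.** More deterioration on placebo, more on QZQG, or a sicker population in both arms can all lead to the same label.
3. **It ignores timing.** A letter opened between day 8 and day 28 counts, although it cannot bias an endpoint already assessed.
4. **It is a cliff.** With 228 patients, 46 openings attach the label. Forty-five do not, even if all fall in one arm of 114 (45/114 = 39%).

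At stake is a randomized comparison that could still be read with a caveat, but would carry the label of a failed trial for reasons unrelated to what it found. Because 'failure' is undefined, someone would have to decide afterwards what follows from it.

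**Working it through.** **Inputs.** From the article: threshold 20%; 228 patients, 1:1, so 114 per arm; planned improvement rates 50% and 70%; two-sided tests. Assumed: all 228 patients as denominator, and every opening rate below, because the article gives none. The 20% itself has no derivation to reproduce.

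**Step 1. Where the rule is met.** 0.20 × 228 = 45.6, so the first count above 20% is 46.

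**Step 2. How often it is met.** With X ~ Binomial(228, p), P(X ≥ 46) is:

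| True opening rate p | P(rule met) |
|---|---|
| 10% | 0.000003 |
| 15% | 0.021 |
| 18% | 0.22 |
| 20% | 0.50 |
| 22% | 0.77 |
| 25% | 0.96 |

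**Step 3. Unequal arms.** Suppose 15% are opened on QZQG and 30% on placebo. The mean is 114 × 0.15 + 114 × 0.30 = 51.3. The variance is 114 × 0.15 × 0.85 + 114 × 0.30 × 0.70 = 38.5, so the SD is 6.2. Simulation gives P(rule met) = 0.82, and the normal approximation, z = (51.3 − 45.5)/6.2 = 0.94, agrees. With 30% in both arms the probability is above 0.999. Benefit thus lowers the chance of the label but does not remove it.

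**Step 4. Overlap with the primary result.** Suppose letters are opened only for patients who do not improve, with probability q in both arms. The expected opening rate is q × (0.5 + 0.3)/2 = 0.4q under 50% vs 70%, and 0.5q under 50% vs 50%. In 200,000 simulated trials with 114 per arm (power 0.87 for the two-sided test):

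| q | 50% vs 70%: significant and labelled failure | 50% vs 50%: labelled failure |
|---|---|---|
| 0.3 | 0.0002 | 0.02 |
| 0.4 | 0.05 | 0.50 |
| 0.5 | 0.44 | 0.96 |
| 0.6 | 0.81 | >0.999 |

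The label can attach to a positive or a negative result, but in this model only when about 40% or more of non-improvers are unblinded. Since it can only remove positive declarations, it cannot raise the type I error.

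**Step 5. The adjacent exclusion.** If unblinded patients are dropped from analysis, take q = 0.5 (20% opened overall). Placebo becomes 0.5/(0.5 + 0.5 × 0.5) = 66.7% and QZQG 0.7/(0.7 + 0.3 × 0.5) = 82.4%. The difference shrinks from 20 to 15.7 points. Unlike the 20% rule, this acts from the first opening.

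**Step 6. Why counting unblinded patients only as not improved is no remedy.** Take 30% opened on placebo and 15% on QZQG, and assume opening is unrelated to improvement. Placebo becomes 0.5 × 0.70 = 35% and QZQG 0.7 × 0.85 = 59.5%. The difference grows from 20 to 24.5 points, in favour of QZQG.

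**The case against.** The strongest reply is that this is a blinding-integrity criterion, set in advance and placed in the allocation section. Nothing in the hypothesis, analysis or population sections refers to it. A reader might infer that it overturns a valid positive or negative result. The article does not support that: it nowhere says the primary test is dropped, reversed or left unreported, and 'valid' begs the question once more than a fifth of patients are unblinded. That part of the reply stands.

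It is also fair that frequent unblinding is not to be expected from the text alone. Section {17b} makes it a safety judgement, section {16a}–{16c} requires prior contact with the sponsor and primary investigator, and critical illness is excluded at entry. At a 10% opening rate the rule is practically never met. The wording that the process will be started and the wording that unblinding is permissible should be reconciled, since they bear on how often the rule could apply.

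Nor does the plan ask for nothing below 20%: each urgent unblinding is recorded and the patient excluded.

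What the reply does not answer is that the sentence as written is a complete rule, with a trigger, a threshold and a whole-trial verdict. Compromised blinding justifies a caveat and sensitivity analyses. It does not undo randomization.

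**Conclusion.** The point holds in a limited form. The protocol labels the entire trial a failure from a rate that ignores arm and timing and, for letter opening, depends on how patients fare. An otherwise interpretable comparison could carry that label whatever its result.

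The size rests on two assumptions, the denominator of 228 and the opening rate. The rule is negligible at 10% or less, met about 1 time in 50 at 15%, an even chance at 20% and nearly certain at 25%. It is worth correcting because the change is cheap, not because the label is likely.

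The exclusion of unblinded patients in the same paragraph needs attention at any opening rate. If it means exclusion from analysis, it conflicts with the ITT definition and selects on outcome. If it means only withdrawal from the study procedures, the text should say so.

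**What to change.** In section {16a}–{16c}, delete the clause that declares the trial a failure, and state instead that:

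- the primary analysis is reported in the prespecified efficacy population (mITT under section {20c}) whatever the unblinding rate;
- unblinding is reported by arm, reason and timing relative to assessment of the primary endpoint, with leakage and letter openings shown separately;
- if more than 20% of randomized patients are unblinded, blinding is reported as compromised and the conclusion is qualified accordingly;
- sensitivity analyses examine patients unblinded before endpoint assessment under more than one assumption, including one unfavourable to QZQG, and not only as not improved.

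In the same edit, reconcile the exclusion instruction with section {20c}, so that unblinded patients otherwise in the analysis population stay in it, in their assigned arm. This concerns analysis only and leaves the patient's clinical handling untouched.

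The cost is a few sentences and a small set of sensitivity analyses. Section {17b} already requires the date, time and reason of each emergency unblinding to be recorded. The small downside is that a poorly blinded trial would be reported with a caveat instead of being voided.

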## Assignment of interventions: blinding

### Who will be blinded after assignment to interventions? {17a}

This is a double-blind trial in which participants, investigators, care providers, outcome assessors, and data analysts are all blinded. Assignment of interventions will only be unblinded after database lock.

### Circumstances and procedure for unblinding if needed {17b}

Unblinding is permissible in emergency situations when investigators believe that it is necessary to perform any agent treatment/action for the trial patient’s safety. To allow emergency unblinding the investigator will be supplied with a set of emergency envelopes. If emergency unblinding of a patient is necessary, an independent pharmacist opens the sealed envelope and informs the investigators of the allocation. And the pharmacist has to enter date and time as well as his/her name and signature on the unblinding form contained in the envelope. Information about the date, time, and reason of unblinding will be recorded in Clinical Case Forms (CRFs) and the envelope.

## Data collection methods

### Plans for assessment and collection of outcomes {18a}

Training sessions on outcome evaluation and data collection will be held for investigators from all centers prior to the start of the study. Investigators are responsible for assessment and collection of outcome, baseline, and other trial data, which are double checked by the data managers and clinical research associates. Nasopharyngeal/oropharyngeal swabs, lower respiratory tract specimens (sputum/tracheal aspirate/bronchial alveolar lavage fluid), and feces/anal swabs will be sent to a central laboratory, where tests will be performed according to laboratory standard operating procedures (SOPs). Data collection forms can be found at http://longhua.site. Three scales (seven-category ordinal scale, the severity scale of 7 influenza-associated symptoms and NEWS2) are used for the outcome measures.

### Plans to promote participant retention and complete follow-up {18b}

During the course of the study, participants may voluntarily withdraw from the trial for subjective or objective reasons at any time. When the subjects request to withdraw, the investigators at study sites must fully inform the importance of continuing to retain and complete the trial, including better observation of drug efficacy and potential adverse reactions, and providing more valuable data for follow-up studies.

## Data management {19}

The doctors in the trial teams will receive training through on-site meetings and remote video to fully understand the protocol and standard operating procedures of this clinical trial. Personnel who participate directly in this trial follow guidelines for Good Clinical Practice (GCP) to ensure the safety of patients, blinding of the study design, data quality, and adherence to the protocol. During the study, an independent Steering Committee will review and supervise all the original documents and CRFs. The PI and medical officers from Longhua Hospital will regularly audit the protocol compliance and enrollment progress through site visits or remote video conference to ensure compliance with the protocol and the data quality at every center. The essential documents (signed informed consent form, follow-up management, CRFs, record of adverse events, number and proportion of missed visits and losses to follow-up) will be monitored and checked for accuracy and completeness by the monitors monthly.

All CRFs will be reviewed by the investigators and independent Steering Committee. The completed CRFs will be securely stored in a locked location and finally sent to two independent data administrators from School of Public Health, Fudan University, who will be responsible for data inspection, entry, and management. When the trial is completed, the Principal Investigator, Sponsor, data administrators, and statisticians will perform a blind review to confirm the dataset. The final database will be locked and analyzed in line with the statistical analysis plan.

## Statistical methods

### Statistical methods for analyzing primary and secondary outcomes {20a}

The primary study analysis will occur when the last patient has either withdrawn or completed day 28 visit, and will be based on cleaned data for all patients up to and including this point. The clinical data will be managed and analyzed by the independent statisticians from a third party (School of Public Health, Fudan University,) in accordance with the statistical analysis plan. Data management and analysis will use SAS V.9.4 (SAS Institute, Cary, NC, USA).

All statistical inferences will be determined using two-sided tests. *P* < 0.05 will be considered significant, and 95% confidence intervals will be used. Data will be described as the mean, standard deviation, and confidence intervals. If necessary, minimum, maximum, P25, P75, and median values will be provided. Paired measurement data will also show the differences between the mean and standard deviation. When using nonparametric methods, median and mean values will be provided. Count data will be described using the frequency distribution and corresponding proportion. Qualitative information will be described using the positive rate, the number of positive cases, and the denominator.

Baseline data analyses (in FAS and PPS) will include demographic indicators and primary and secondary outcomes before intervention. Measurement data will be described using a *t*-test or *t*’ test (if the variance is absent). Count data will be described using the Pearson’s *χ*^2^ test. Rating data will be described using the two-sample Wilcoxon rank sum test.

Logistic regression model will be used to explore the efficacy (*QZQG* group and placebo group) and factors affecting efficacy. Dependent variable is the proportion of clinical improvement at day 7. In addition to drugs, independent variables also include the basic information and life behavior factors of participants. The basic information includes gender, height, weight, age, and underlying diseases that include chronic obstructive pulmonary disease, asthma, diabetes, hypertension, hyperlipidemia, hyperuricemia, cardiovascular disease, autonomic nervous dysfunction, lung cancer, other tumors, etc. Life behavior factors mainly include smoking and drinking.

For the efficacy analyses of quantitative variables, comparisons between groups will use repetitive measure analysis of variance and covariance analysis. For qualitative variables, comparisons between groups will use the Pearson’s *χ*^2^ test and center effect analysis will use the Cochran-Mantel-Haenszel (CMH) test. For rating variables, group comparisons will be tested by the Kruskal-Wallis test and the central effect analysis will be tested by the CMH test or grade logistic regression. For center effect analysis, the generalized linear model (GLM) and CMH methods will be used for quantitative and qualitative indicators, respectively. A logistic regression model will be performed for the evaluation and correction of rating variables. For safety analysis, the prevalence of adverse events in the two groups will be compared using the Pearson’s *χ*^2^ test, as well as listing and describing the events that occur during the trial. A description of laboratory test results, electrocardiograph, and chest radiograph will be described as normal/abnormal changes, as well as the relationship between the abnormal changes and the test drug; these changes will be stated.

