#### Secondary outcome measure

Secondary outcomes are the following:
Time to clinical improvement of symptoms (TTCIS) [time frame: baseline to day 14].Participants assessed the severity of 7 influenza-associated symptoms (cough, sore throat, headache, nasal congestion, feverishness/chills, muscle/joint pain, and fatigue) on a 4-point scale (0 = no symptoms, 1 = mild, 2 = moderate, and 3 = severe). TTCIS was defined as the time from the start of treatment to the time when all influenza symptoms were alleviated, as defined below, for a duration of at least 21.5 h:• Pre-existing symptoms (cough, fatigue, or muscle/joint pain that existed prior to influenza) that were worse at baseline must have improved at least 1 point from baseline.• New symptoms must have alleviated, defined as a symptom score of none (0) or mild (1).Time to defervescence (TTD) [time frame: baseline to day 14].Time to defervescence includes defervescence onset time and the time to complete defervescence. Defervescence onset time is defined as the time from the start of treatment to the time when the body temperature decreases to ≤37.3 °C. And complete defervescence is defined as the time from the start of treatment to the time when the temperature of ≤37.3 °C sustained for ≥ 24 h [14, 28].Percentage of participants with 2 or more Influenza-related complications [time frame: baseline to day 28].Secondary influenza complications include pneumonia, encephalitis, meningitis, encephalopathy, myelitis, Guillain-Barré syndrome, myocarditis, pericarditis, myositis, and septic shock.Percentage of participants whose symptoms were improved at each time point [time frame: 12, 24, 36, 48, 72, 96, 120, 144, and 168 h after the initial dose of study treatment]. The criteria for improvement of influenza symptoms have been described above.Percentage of participants reporting normal temperature at each time point [time frame: 12, 24, 36, 48, 72, 96, 120, 144, and 168 h after the initial dose of study treatment]. Defined as the percentage of participants whose axillary body temperature dropped to equal or less than 37.3 °C after the initiation of the study treatment.Body temperature at each time point [time frame: 12, 24, 36, 48, 72, 96, 120, 144, and 168 h after the initial dose of study treatment]. Participant’s self-measured axillary temperature using an electronic thermometer.Percentage of participants requiring systemic antibiotics for infections secondary to influenza [time frame: day 2 to day 28].Percentage of participants with adverse events (AEs).Inpatient length of stay defined as number of days in hospital [time frame: day 2 to day 28].Median time (days) receipt of oxygen [time frame: day 2 to day 28].

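### Symptom-alleviation and defervescence times are followed only to day 14, yet the one stated method that can cover them is ANOVA/covariance analysis, which cannot use an unresolved patient's time

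*Protocol article*

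**What the plan says.** The Protocol article, Secondary outcome measure, lists two time outcomes first: "Time to clinical improvement of symptoms (TTCIS) [time frame: baseline to day 14" and "Time to defervescence (TTD) [time frame: baseline to day 14". The definition is that "TTCIS was defined as the time from the start of treatment to the time when all influenza symptoms were alleviated", with alleviation lasting at least 21.5 h. Defervescence has an onset time and a complete time, both counted from start of treatment. Two durations with a day-28 horizon follow: "Inpatient length of stay defined as number of days in hospital", and the median time on oxygen.

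Statistical methods {20a}, headed as covering primary and secondary outcomes, gives three rules:
- Quantitative: "For the efficacy analyses of quantitative variables, comparisons between groups will use repetitive measure analysis of variance and covariance analysis".
- Qualitative: "For qualitative variables, comparisons between groups will use the Pearson’s *χ*^2^ test and center effect analysis will use the Cochran-Mantel-Haenszel (CMH) test".
- Rating: "For rating variables, group comparisons will be tested by the Kruskal-Wallis test".

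The only rule for incomplete data is in {20c}: "Multiple imputation will be used for missing data". Kaplan-Meier, log-rank, Cox and censoring do not appear, nor does a rule for deaths in the time outcomes. Death is foreseen as category 7 of the ordinal scale under Primary outcome measure.

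**The concern.** A patient whose symptoms or fever have not resolved by day 14 has no event time, but the time is not unknown in the ordinary sense: it is longer than 14 days. Repeated-measures ANOVA expects several values per patient. Covariance analysis accepts one value but needs it to be complete. Neither can take in a lower bound. The general imputation sentence does not separate such a patient from one whose record is missing.

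The slowest patients carry much of the treatment contrast. If they drop out of the comparison, the arms look more alike than they are. These outcomes matter because the Discussion says the secondary endpoints are there to show consistency with the primary one, and Sample size {14} makes later comparisons exploratory only when the initial hypothesis is not rejected.

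Length of stay and oxygen time have a different weakness. Scored as plain day counts, they give a patient who dies early a short and apparently favourable value.

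**Working it through.** **Which rule applies.** The three times are neither proportions nor ordered grades, so the qualitative and rating rules do not fit. Only the quantitative rule is left. The outcome that fits repeated-measures ANOVA naturally is body temperature, taken at nine time points from 12 to 168 h.

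**Inputs.** The day-14 horizon is from Secondary outcome measure, and 101 patients per arm is from Sample size {14}. The article gives no event-time rates and no figure of its own to reproduce here, so exponential times and the medians below are assumptions, shown over a range.

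**Formulas.** For median m:
- Share unresolved at day 14: S = 0.5^(14/m).
- True mean: m/ln 2.
- Mean among patients with an event by day 14: m/ln 2 − 14·S/(1 − S).

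**Numbers.**
- m = 7: S = 0.5^2 = 0.25; event-only mean 10.10 − 14 × 0.25/0.75 = 5.43 days.
- m = 5: S = 0.5^2.8 = 0.144; 7.21 − 14 × 0.144/0.856 = 4.87 days.
- m = 4: S = 0.5^3.5 = 0.088; 5.77 − 14 × 0.088/0.912 = 4.41 days.
- m = 3: S = 0.5^4.67 = 0.039; 4.33 − 14 × 0.039/0.961 = 3.75 days.
- m = 2: S = 0.5^7 = 0.008; 2.89 − 14 × 0.008/0.992 = 2.78 days.

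**Ratios of means, treated to control.**
- 7 vs 5 days: true 5/7 = 0.71; event-only 4.87/5.43 = 0.90.
- 5 vs 4 days: true 4/5 = 0.80; event-only 4.41/4.87 = 0.91.
- 3 vs 2 days: true 2/3 = 0.67; event-only 2.78/3.75 = 0.74.

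**Power.** Simulation: 101 per arm, 2000 runs, assumed hazard ratio 1.5, two-sided 5%, no deaths or dropout. The t-test stands for a two-group ANOVA.

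| Control median (days) | Controls unresolved at day 14 | t-test, events only | t-test, non-events set to day 14 | Log-rank |
|---|---|---|---|---|
| 3 | 4% | 64% | 79% | 79% |
| 5 | 14% | 36% | 76% | 79% |
| 7 | 25% | 22% | 69% | 73% |
| 10 | 38% | 12% | 60% | 65% |

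The event-only mean difference shrinks from −2.40 to −0.85 days at a median of 5, and from −3.37 to −0.70 days at a median of 7. With identical arms (hazard ratio 1), the event-only t-test rejects in 4.45% to 5.3% of runs.

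**The case against.** The strongest reply is that {20a} never names these outcomes. Its quantitative rule reads as if written for body temperature, the same section foresees nonparametric methods, oxygen time is already named as a median, and the analysis follows a statistical analysis plan that is not shown. Censoring and death rules are commonly left to such a plan. It is true that the placement is by elimination. But the article does more than stay silent: it assigns one method to all quantitative efficacy variables, without exception, under a heading that includes the secondary outcomes. A plan that followed it would inherit the misfit.

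Several stronger readings are tempting and not supported:
- *Unresolved or deceased patients will be imputed or dropped.* The article says neither. The attenuation above depends on dropping them. Setting non-events to day 14 would keep power close to log-rank, but no such rule is stated.
- *The p-values would be invalid.* With identical arms the event-only comparison kept its error rate near 5%. What is shown is attenuation and lost power.
- *All the time outcomes are cut off at day 14.* Length of stay and oxygen time run to day 28.
- *The arm with more early deaths would gain.* This could happen for stay and oxygen time, but the article gives no death rate, and eligibility excludes critically ill patients at entry, so no size can be given.
- *Events after day 7 cannot be dated.* Table 2 lists symptom and temperature records for days 1 to 7 and next at day 14. Under medians of 4, 5 and 7 days, about 21% to 25% of patients have their event in that gap. However, a diary card is issued at screening, and its content is not shown.

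**Conclusion.** The point holds for TTCIS and both defervescence times: the stated method, reached by elimination, does not suit a time to event with a fixed horizon. The size depends on how many patients are unresolved at day 14, which the article does not let one estimate. Under exponential times it ranges from a modest loss at a 3-day control median to losing most of the apparent effect at 7 days or more, provided that only observed times are compared. For length of stay and oxygen time the narrower point holds that deaths need a scoring rule. The primary outcome is binary and untouched, so this is a correction that should be made to supportive analyses, not a threat to the main conclusion.

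**What to change.** In Statistical methods {20a}:
- Limit repeated-measures ANOVA to variables measured repeatedly, such as body temperature.
- Analyse TTCIS and both defervescence times with Kaplan-Meier curves, a log-rank test stratified by centre (matching the randomisation) and a Cox hazard ratio with 95% CI.
- Censor event-free patients at day 14 or last contact, and keep deaths in the risk set to day 14 as never resolved.
- State in {20c} that a patient event-free at day 14 is not missing and is not imputed.
- Keep the definitions of length of stay and oxygen time, but analyse them so that an early death is not a favourable value, for example a worst-rank score for death in a centre-stratified Wilcoxon test. Other death rules are defensible if fixed in advance.

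The cost is protocol and analysis-plan wording, plus standard procedures in the SAS software already named. No new data are needed. The wording should be settled before unblinding.
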